### Intervention

#### JLJ granules group

Patients randomly classified into the JLJ granules group will be provided with Jianpi Lishi Jiedu granules. Administration method: A pack of granules (110 g/pack) is dissolved into 150 ml of warm water every day and divided into 2 equal doses for administration at 2 separate times. The JLJ granules are produced by Tiangjiang Pharmaceutical Co., Ltd. (Jiangyin), with a herbal formula comprising 15 g of pilose asiabell roots, 10 g of fried *Atractylodes macrocephala*, 30 g of glabrous greenbrier rhizome, 15 g of *Forsythia suspensa*, 30 g of honeysuckle stem, and 10 g of *Cynanchum roseum*.

#### Placebo control group

Patients in the control group will be provided with placebo control granules. The administration method will be the same as with the JLJ granules. The dosage of each pack of placebo control granules must also be 110 g. The main components of the placebo control granules include starch, maltodextrin, caramel pigment, etc., free from any therapeutic effect.

### Study period

The course of intervention is set as 3 months. Follow-ups will be conducted at months 3, 6, and 12, and clinical data will be recorded again, and the reexamine of colonoscopy will be undergone at month 12. A safety evaluation will be carried out for all the patients after treatment initiation (comprising blood routine, urine routine, stool routine, liver and kidney function, and electrocardiography).

### Outcomes

#### Primary outcome

The primary outcome of this study is the recurrence rate of CRA within 12 months: refer to the Diagnostic Criteria and Therapeutic Effect for Diseases and Syndromes in Traditional Chinese Medicine (Chinese Medicine Industry Standards of the People's Republic of China; ZY/T001.1–94); recurrence refers to the formation of new adenomatous lesions after complete resection of the initial lesions, appearing at the original affected site or at other sites. The recurrence rate of adenomas = the number of patients with recurrence/the number of intra-group patients × 100%. The size, number, location, pathological type, etc. of CRAs will also be recorded.

#### Secondary outcome

Cardinal and minor TCM symptom scores: refer to “Guidance principle of clinical study on new drug of traditional Chinese medicine” [20]. The scores and details of TCM syndrome are provided in Table 1Bristol Stool Scale [21]: type 1: the stool forms separate hard lumps and is difficult to pass; type 2: the stool is sausage-shaped, with a lumpy surface; type 3: the stool is strip-shaped, with cracks on the surface; type 4: the stool is strip-shaped, soft and smooth; type 5: the stool forms soft lumps; type 6: the stool is mushy; type 7: the stool is watery.Safety indicators: including blood routine, urinalysis, stool routine, liver and kidney functions, and electrocardiographyThe efficacy of TCM symptoms: refer to the Diagnostic Criteria and Therapeutic Effect for Diseases and Syndromes in Traditional Chinese Medicine (Chinese Medicine Industry Standards of the People’s Republic of China; ZY/T001.1–94)Clinical control: After treatment, symptoms and signs almost disappeared and patients returned to normal activities and work. The efficacy rate for syndromes is ≥90%.Excellent efficacy: After treatment, the signs and symptoms and the results of examinations improved significantly. The efficacy rate for syndromes is ≥60% but < 90%.Efficacy: After treatment, improvement of the symptoms and signs and examination results was observed. The efficacy rate for syndromes is ≥30%, but < 60%.Lack of efficacy: After treatment, symptoms and signs and the results of examinations did not improve compared to before the treatment. The efficacy rate for syndromes was < 30%.Blinding assessment: To determine whether the blind is successful, all of the cases will be asked to guess which drug (JLJ granule, placebo granule, uncertain) they have received at months 0, 3, and 6 and month 12, and relevant results will be recorded by the statistician from the third-party statistical agency. If participants do not choose “uncertain,” the reason why they had made that assumption will also be recorded.

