### Objective and hypothesis

This study’s principal objective is to assess the recurrence of CRA, conduct an evaluation of the clinical efficacy of JLJ granules in the treatment of postoperative patients with CRA, and explore the safety profile of JLJ granules in the treatment of postoperative patients with CRA. In this study protocol, it will be assumed that, compared with the placebo, JLJ granules have better effects in terms of the recurrence rate of CRA, major symptom alleviation, the remission rate of minor symptoms, the Bristol stool scale, and the efficacy for patients with CRA after surgery, with no significant adverse effects despite an adequate safety profile.

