**Cardinal TCM symptom**				
Diarrhea or mucus	None	Diarrhea or mucus, defecate 3–4 times/day	Diarrhea or mucus, defecate 5–10 times/day	Diarrhea or mucus, defecate>10 times/day
Constipation	None	Dry stool, defecate 1 time/day	Dry stool, defecate once/2–3 days	Very dry stool, defecate once/5–7 days
Abdominal pain	None	Occasionally, mild abdominal pain	Sometimes, moderate abdominal pain	Often, severe abdominal pain
Abdominal distension	None	Occasionally, mild abdominal distension	Sometimes, moderate abdominal distension	Often, severe abdominal distension
Inappetence	None	Mild, less than 1/3 reduction in food intake	Moderate, more than 1/3 reduction in food intake	Severe, no eating all day long
Dry or sticky feeling in the mouth	None	Mild, occasionally	Moderate, sometimes	Severe, often

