### Statistical analysis

All data will be entered and counted by professional statisticians using SAS 9.4 (SAS Institute Inc., Cary, NC, USA) and SPSS 26.0 (IBM, Armonk, NY, USA). If the data is normally distributed and the variance is uniform, the measurement data will be expressed as mean ± standard deviation (*x* ± *s*). The paired *t*-test will be adopted for intra-group comparison before and after treatment, and the independent sample *t*-test will be adopted for inter-group comparison before and after treatment. If the data does not follow a normal distribution or has an uneven variance, the measurement data will be expressed as median (quartile interval) [M (Q)], and the Wilcoxon rank sum test will be employed for data analysis before and after treatment. The chi-square test will be adopted to compare the rates between both groups. *P*<0.05 means that the difference is statistically significant.

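### The Bristol Stool Scale hypothesis has no defined direction: on the raw 1–7 type, improvements in constipated and diarrhoeal patients can offset each other

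*Protocol article*

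**What the plan says.** The Secondary outcome section describes the seven stool types. One end is "type 1: the stool forms separate hard lumps and is difficult to pass", the other is "type 7: the stool is watery", and the middle is "type 4: the stool is strip-shaped, soft and smooth". It gives no target range, responder definition or direction of benefit for the scale.

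The Objective and hypothesis section expects JLJ to do better than placebo on several measures, including "the Bristol stool scale, and the efficacy for patients with CRA after surgery".

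Table 1 lists diarrhoea and constipation as separate cardinal symptoms. Moderate diarrhoea is "Diarrhea or mucus, defecate 5–10 times/day" and moderate constipation is "Dry stool, defecate once/2–3 days". Under the Inclusion criteria, two of the six cardinal items and one minor item are enough for entry.

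The Statistical analysis section is generic. If normality and equal variance hold, "the measurement data will be expressed as mean ± standard deviation" and t-tests are used; otherwise medians and the Wilcoxon rank sum test. Rates are compared by chi-square. The Bristol scale is not assigned to any of these.

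**The concern.** On a scale whose desirable value lies inside it, better is neither higher nor lower. A constipated patient who improves moves up the scale and a diarrhoeal patient who improves moves down. A t-test or rank test on the raw type only detects a shift in one overall direction, so in a mixed population it can miss a real move towards the middle.

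Two things are at stake. The planned comparison may show little when JLJ normalises stool in many patients. And while the measure stays undefined, raw mean, distance from the middle and proportion in a range all remain open to choice once results are known.

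**Working it through.** The protocol states no figure for this outcome, so there is nothing to reproduce. The check is of the mechanism and its size.

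**Inputs from the protocol:** types 1 to 7 (Secondary outcome); both stool patterns eligible (Inclusion criteria, Table 1); 40 per arm, or 33 per arm from the 66 before dropout inflation, and two-sided 0.05 (Sample size).

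**Assumed, because the protocol does not give them:** constipated patients start near type 2 and diarrhoeal patients near type 6; type 4 is the centre of the desirable range; a share *f* of patients is constipated; 60% normalise on JLJ and 20% on placebo.

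**Step 1: everyone improves fully to type 4.** Mean raw change = 2*f* − 2(1 − *f*) = 4*f* − 2. For *f* = 0, 25, 50, 75 and 100% this is −2, −1, 0, +1 and +2. Distance from type 4 falls by 2 in every case.

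**Step 2: expected difference between arms, before scatter.** If a proportion *p* normalises, the arm mean of the raw type is 4 + (1 − *p*)(2 − 4*f*). JLJ minus placebo is then −(0.6 − 0.2)(2 − 4*f*) = −0.8(1 − 2*f*):

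- *f* = 0: −0.80
- *f* = 10%: −0.64
- *f* = 25%: −0.40
- *f* = 50%: 0

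Mean distance from type 4 is 2(1 − 0.6) = 0.8 on JLJ and 2(1 − 0.2) = 1.6 on placebo. The difference is −0.8 at every *f*.

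**Step 3: simulated power for the same scenario, 40 per arm, with scatter added.**

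| Constipated share | Raw type, t-test | Raw type, Wilcoxon | Distance from type 4 |
|---|---|---|---|
| 0% | 85% | 85% | about 82% |
| 10% | 56% | 69% | about 82% |
| 25% | 21% | 31% | about 82% |
| 50% | 5% | 6% | about 82% |

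The level of these figures depends on the scatter assumed around types 2, 4 and 6. A parallel run of the scenario gave raw-type power of 82%/82%, 51%/62%, 20%/28% and 6%/6% at the same shares, with 74–76% for distance. In that run, chi-square on the proportion with types 3–5 kept about 70% at every mix.

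**Step 4: a different effect model.** Here all patients drift towards type 4, by 0.3 types on placebo and 1.3 on JLJ, with SD 1 and rounding to 1–7. At 40 per arm the raw-type t-test/Wilcoxon power is 99%/99%, 76%/89%, 29%/47% and 5%/6% at shares of 0, 10, 25 and 50%. Distance from type 4 gives 95–96% throughout. At 33 per arm it gives 92–93%, and the raw type shows the same fall.

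The pattern is stable across models. The raw type does as well as distance, or slightly better, when only one stool pattern is present; it loses most of its power at a one-quarter minority and all of it at an even mix.

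**The case against.** The strongest reply is that the protocol never says the Bristol type will be compared as a raw score. Its categories are called types, and chi-square for rates is also listed. A comparison of the proportion in a given range would fit the text: with 60% versus 20% normalised and no misclassification, chi-square has about 96% power at 40 per arm. The derivation of a secondary scale may also sit in an analysis plan that is not shown.

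This stands in part. The raw-type comparison is the natural reading, not a stated plan. But no Bristol rate is defined, although the same section gives explicit percentage cut-offs for TCM symptom efficacy. And the hypothesis itself is in the document: it claims an improvement on a scale without saying what improvement is.

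Three further limits also stand:

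- **Case mix.** A reader might infer that improvements will cancel out. The protocol does not support that. Patients can qualify on abdominal pain, distension, appetite or mouth symptoms with no stool disorder, and nothing shows that both stool patterns will enrol in number. The loss runs from none to complete.
- **False differences.** A reader might also infer that an uneven mix of constipation and diarrhoea between arms would create spurious effects. Under randomisation that is chance imbalance, which the type I error already covers; a simulated null with a random mix of types 2 and 6 rejected in 5.1% of runs.
- **Other capture.** Table 1 scores diarrhoea and constipation separately with 0 as best, so the cardinal symptom score registers improvement in either direction. That softens the consequence but does not define the Bristol outcome, which is listed and hypothesised on its own.

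**Conclusion.** The concern holds as a matter of definition. The protocol hypothesises a better result on a scale that is abnormal at both ends, in a population open to patients at both ends, and the methods it lists most naturally lead to the raw type. Under the assumed 60% versus 20% normalisation with 40 per arm, raw-type power is about 85% with no constipated patients, 21–31% at one quarter and 5–6% at an even mix, against about 82% for distance from type 4 throughout. These figures rest on an assumed effect, scatter, starting types and case mix.

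The protocol does not fix a wrong test, and the primary outcome is untouched. This is a secondary outcome that should be corrected; it does not threaten the trial's main conclusion.

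**What to change.** Before unblinding, state what a better Bristol result is, in one of two ways:

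- distance from type 4, |type − 4|, compared between arms with adjustment for the same measure at baseline; or
- the proportion of patients with types 3–5, compared with the chi-square test already listed.

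Show the raw type only descriptively, split by baseline stool pattern (constipated, diarrhoeal, neither).

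The cost is a sentence in the Outcomes section and one in the Statistical analysis section, or an entry in the analysis plan. Both options use data already being recorded. The first needs a baseline-adjusted model that the article does not list; the second needs no new test.

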### Inclusion criteria

Patients diagnosed with colorectal polyps through colonoscopy and adenoma through histopathological examination and received resection of the adenoma with biopsy clips or endoscopic resection within 4 weeks, including snare polypectomy (SS), endoscopic mucosal resection (EMR), piecemeal EMR (pEMR), endoscopic submucosal dissection (ESD), etc.Patients with TCM syndromes of spleen-asthenia with excessive damp; refer to “Guidance principle of clinical study on new drug of traditional Chinese medicine” [20]. The clinical symptoms of spleen-asthenia with excessive damp are stated in Table 1. The cardinal symptoms in line with 2 items and the minor symptoms in line with 1 item shall be diagnosed as spleen-asthenia with excessive dampPatients with age ranging from 18 to 65 years old, regardless of genderPatients that voluntarily accepted observation and signed the informed consent and ethical principles

**Table 1 Tab1:** The scores of TCM syndrome

Symptoms	Scores of TCM symptoms			
	None	Mild	Moderate	Severe
	0	1	2	3

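### Percentage bands on low integer symptom scores make the TCM efficacy grade coarse; the month-3 total score adjusted for week 0 should carry the symptom-efficacy conclusion

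*Protocol article*

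**What the plan says.** Table 1 (Inclusion criteria) scores six cardinal and three minor symptoms as integers from 0 to 3, so the total runs from 0 to 27. The entry rule is "The cardinal symptoms in line with 2 items and the minor symptoms in line with 1 item shall be diagnosed as" the required syndrome. It sets no minimum severity, so a patient with three mild symptoms enters with a total of 3.

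The Secondary outcome section lists the cardinal and minor symptom scores as one outcome and the efficacy of TCM symptoms as another. The second has four grades, attributed to a national TCM standard:

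- *Clinical control*: "The efficacy rate for syndromes is ≥90" per cent
- *Excellent efficacy*: "The efficacy rate for syndromes is ≥60% but < 90" per cent
- *Efficacy*: "The efficacy rate for syndromes is ≥30%, but < 60" per cent
- *Lack of efficacy*: "The efficacy rate for syndromes was < 30" per cent

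The article does not print the formula for the rate, or say whether it uses the total, cardinal or minor score.

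For tests, the Statistical analysis section says: "The chi-square test will be adopted to compare the rates between both groups". Measurement data get an independent-sample t-test between groups, or a Wilcoxon test if the data are not normal or the variances differ. No adjustment for the week-0 score is mentioned. The Objective and hypothesis section names efficacy among the expected benefits, beside recurrence, symptom relief and stool form.

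**The concern.** A percentage cut-off on a small integer can be met only in whole points. The relief needed to reach a grade therefore jumps from one starting score to the next, and patients with the same absolute relief can fall on different sides of a boundary. Banding also discards differences within each band.

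The trial plans 40 patients per arm and allows for 15% dropout, so little information can be spared. The grade and the raw scores both bear on symptom benefit, and the article does not say which one carries the conclusion. The only test it offers for categorical outcomes, chi-square, ignores the order of the grades.

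**Working it through.** **No figure to reproduce.** The article states no power or error rate for the efficacy grade.

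**Inputs from the article.** Items scored 0 to 3; lowest eligible total 3; cut-offs at 30, 60 and 90%; 40 per arm with 15% dropout, so 40 × 0.85 = 34 evaluable; two-sided 0.05.

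**Assumption.** Rate = (total before − total after) / total before × 100%.

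**Step 1: points needed for at least *Efficacy*.** This is the smallest whole number not below 0.30 × b, where b is the starting total.

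| b | 0.30 × b | Points needed | One point fewer gives |
|---|---|---|---|
| 3 | 0.9 | 1 (1/3 = 33.3%) | 0% |
| 4 | 1.2 | 2 (2/4 = 50.0%) | 1/4 = 25.0% |
| 5 | 1.5 | 2 (2/5 = 40.0%) | 1/5 = 20.0% |
| 6 | 1.8 | 2 (2/6 = 33.3%) | 1/6 = 16.7% |
| 7 | 2.1 | 3 (3/7 = 42.9%) | 2/7 = 28.6% |

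Over a wider range, three points of relief is *Clinical control* from 3, *Excellent efficacy* from 4 or 5, *Efficacy* from 6 to 10, and *Lack of efficacy* from 11 upwards.

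**Step 2: the jump remains when relief is proportional to severity.** Let each point resolve independently with probability 0.30, the same for every patient. The chance of reaching 30% is then the binomial probability of at least the points needed:

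- b = 3: 1 − 0.7³ = 0.657
- b = 4: 1 − 0.7⁴ − 4 × 0.3 × 0.7³ = 1 − 0.2401 − 0.4116 = 0.348
- b = 5: 0.472
- b = 6: 0.580
- b = 7: 0.353

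The pattern is a sawtooth, not a trend.

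**Step 3: power, on assumed distributions.** None of these inputs is in the article. With 34 per arm, patients have 3, 4, 5 or 6 symptoms at entry (probabilities 0.35, 0.30, 0.20, 0.15) of severity 1, 2 or 3 (0.6, 0.3, 0.1). Each absent symptom has a 5% chance of appearing. Each point resolves with probability 0.30 on placebo and 0.45 on active treatment.

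| Analysis | Power |
|---|---|
| Chi-square, four grades | about 57% |
| Rank test, four grades | about 72% |
| t-test on month-3 total, unadjusted | about 57% |
| t-test on change in total, unadjusted | about 68% |
| Month-3 total adjusted for week 0 (ANCOVA) | about 83% |

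Repeat runs moved these by one or two percentage points.

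**Step 4: other assumptions.** A second model, also with 34 per arm, set the mean starting total at about 7, 10 or 13.

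- Relief independent of baseline (2.0 v 3.4 points): ANCOVA 67–72%, four-grade chi-square 31–38%, rank test on grades 45–53%. The change-score t-test was level with ANCOVA (68–72%).
- Relief proportional to baseline (30% v 42%): ANCOVA 50–87%, chi-square 26–61%, rank test 38–75%.

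The adjusted score beat every analysis of the grade in every scenario. The margin varied.

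**Step 5: bias and what the grade tracks.** With no drug effect, rejection rates for the grade stayed between about 3% and 6%. In the Step 3 model the rank correlation of grade with starting score was 0.01 to 0.03, and with points relieved 0.75 to 0.79. In the second model it was about −0.3 (baseline-independent relief) or −0.02 to −0.05 (proportional relief) with starting score, and 0.67 to 0.84 with points relieved.

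**The case against.** The strongest reply is that a percentage is meant to scale with baseline, so calling equal points identical relief prefers one scale over another. That is fair, and it rules out a reading that a reader might take from the 3-versus-4 example: that the grade measures baseline as much as benefit. The correlations in Step 5 contradict it. Nor are the two patients graded as opposites, since their grades are adjacent. What survives is the sawtooth in Step 2, which whole-point scoring produces even under proportional relief.

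A second reply is that much of the power gap is not due to the bands. This also stands in part. In the Step 3 model the unbanded percentage had 76–78% power, so with a rank test the bands cost only about 5 points. The four grades under a rank test beat both unadjusted t-tests on the raw score. Most of the gain over the raw-score tests therefore comes from baseline adjustment, and the rest of the loss comes from using chi-square on ordered grades.

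Third, the formula and the standard are not visible, and the article states no 30% responder threshold. The arithmetic is therefore conditional on the usual formula, and no responder analysis should be attributed to the plan. The article does, however, state its tests: chi-square for rates and unadjusted comparisons for scores.

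Finally, the outcome is secondary and the raw scores are also analysed. That limits the consequence but leaves the priority between the two unsettled.

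**Conclusion.** The point holds as a matter of efficiency. If the rate is the percentage fall in the summed score, the bands are coarse at totals that the entry rule admits, and the grade depends partly on the starting integer. That arithmetic needs no further assumption. The power loss does: about 57% with a four-grade chi-square, and 57% or 68% with the unadjusted t-tests, against about 83% for the adjusted total. These figures rest on assumed baseline and relief distributions. The advantage of the adjusted score over the grade kept its direction throughout; its advantage over the change score vanished when relief did not depend on baseline.

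A reader might infer that the grade biases the comparison between arms. The documents do not support that: randomisation balances starting scores on average, and the simulated error rates are near nominal. The primary outcome, adenoma recurrence, is unaffected.

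**What to change.** In the Statistical analysis section, state that the main symptom-efficacy analysis is the between-arm difference in total TCM symptom score (cardinal plus minor) at month 3, adjusted for the week-0 total by ANCOVA. Report the four grades as supportive, either descriptively or with an ordinal rank test in place of chi-square. While editing that text, state the rate formula and the score it uses.

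The cost is a sentence or two. Both scores are already collected at week 0 and month 3. The downside is that the customary TCM grade no longer carries the efficacy claim on its own, which may matter for comparison with other TCM trials; keeping the grades in the report preserves most of that.

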### Randomization

In this clinical trial, 80 postoperative patients with CRA will be randomly distributed into a JLJ granule (treatment) group or the placebo control group in a ratio of 1:1, according to the randomized sequence table generated by SAS 9.4 (SAS Institute Inc, Cary, NC, USA), with each patient attributed a number ranging from 01 to 80; each of these codes is unique to a specific patient. The test designer will decide the number series for the JLJ granule group and the control group. JLJ granules and placebo granules will be numbered and labeled with the same serial numbers as described above. An independent statistician from a third-party statistical agency, the trial designer, and the drug administrator will participate in the randomization, but will not be involved in the study process and the statistical analysis of the test results.

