### Allocation concealment and blinding

The drug administrator will number the outer packages of drug packaging based on a random numerical sequence table. The independent statistician will prepare the allocation sequence table based on the above randomization and random numerical table, encrypt the computer software, and make 3 copies. Said copies will be kept by the independent statistician, the trial designer, and the drug administrator, respectively. The random numerical table, allocation sequence table, and numbers selected by relevant patients will be sealed in opaque envelopes. Before the trial completion, the group allocations will be masked, and all the patients, clinicians, nurses, data managers, statisticians, and other personnel will be blinded to the trial, and the random sequence table and number must be kept strictly confidential. The blinding can only be uncovered with the consent of the main researchers after completion of the trial and data analysis or in case an emergently severe adverse event occurs. Placebo and JLJ granules will be both packed in opaque packages, which will be exactly the same in appearance, color, smell, taste, dosage, and packaging. For emergency unblinding during the study, relevant cases will be considered as dropped out.

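### The statistician who, on the natural reading, makes and keeps the allocation table is also assigned to record patients' treatment guesses, which conflicts with that person's stated separation from the study

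*Protocol article*

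**What the plan says.** Three sections of the protocol article describe the role of a statistician from outside the trial team.

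- **Randomization:** "An independent statistician from a third-party statistical agency, the trial designer, and the drug administrator will participate in the randomization". The same sentence says that these people "will not be involved in the study process and the statistical analysis of the test results".
- **Allocation concealment and blinding:** "The independent statistician will prepare the allocation sequence table based on the above randomization and random numerical table". Three copies are made: "Said copies will be kept by the independent statistician, the trial designer, and the drug administrator, respectively". This section also counts statisticians, without exception, among the personnel to be kept blinded until the trial is complete.
- **Secondary outcome (blinding assessment):** the recorder is named here: "relevant results will be recorded by the statistician from the third-party statistical agency". The question put to patients is which drug "they have received at months 0, 3, and 6 and month 12". For patients who commit to a guess, "the reason why they had made that assumption will also be recorded".

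Two other sections bear on the point. Participants assigns data collection to two trained researchers. Study design places the baseline record (week 0) before the intervention starts and the colonoscopy at month 12.

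**The concern.** The blinding assessment is a listed secondary outcome, and its stated purpose is to show whether masking succeeded. Such a check is most credible when whoever handles the answers cannot know which answers are correct. Here the recorder named is, as far as the text shows, a holder of the code.

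Three things are at stake.

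- **Consistency of roles.** Recording a secondary outcome at four points in follow-up is part of running the study. The Randomization section says that this statistician takes no such part.
- **Credibility of the blinding result.** A recorder who knows the allocation could, even without intent, classify vague answers or write up reasons differently by arm. The free-text reasons leave most room for this.
- **What the four rounds can show.** The month-0 answer comes before any drug has been taken. The month-12 answer falls at the same time point as the colonoscopy, and the order is not stated.

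The TCM symptom scores and stool type rest largely on patient report, so readers will look to the blinding assessment when they judge those outcomes.

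**Working it through.** No sample size, power or event figure is involved, so the check is mainly a comparison of the sections.

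**Step 1: is it the same person?** Randomization introduces a statistician from a third-party statistical agency, with an indefinite article. Allocation concealment and blinding then refers to the independent statistician as someone already introduced. Secondary outcome refers to the statistician from the third-party statistical agency, with a definite article and the same description of the employer. No second statistician from that agency is described. Oversight and quality control mentions a third-party testing institution whose investigators record data on site, but that body has a different name and no statistician is mentioned there. One person is therefore the natural reading. It remains an inference, because the article never says so outright.

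**Step 2: set the role rules side by side.**

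| Rule | Section | Consequence for this statistician |
|---|---|---|
| Takes part in randomization | Randomization | Has access to allocation |
| Prepares the allocation table and keeps one of three copies | Allocation concealment and blinding | Holds the code |
| Stays out of the conduct and analysis of the study | Randomization | Should not record outcomes |
| Statisticians are blinded until trial completion | Allocation concealment and blinding | Cannot be true of the person who made the table |
| Records guesses and reasons at four time points | Secondary outcome | Records an outcome during follow-up |

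The third and fifth rows cannot both hold for one person. The second and fourth cannot both hold either, unless the fourth is meant only for other statisticians, which the text does not say.

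**Step 3: count the exposure.** Inputs: 80 patients (Study design) and 4 time points (Secondary outcome).

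- Planned records: 80 × 4 = 320. This is a ceiling, since the Sample size section allows for 15% dropout.
- Month-0 records, before any drug: 80 × 1 = 80.
- Planned records after treatment has begun: 320 − 80 = 240, again a ceiling.

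These are counts of forms. They say nothing about the size or direction of any bias.

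**Step 4: timing of the rounds.**

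- Month 0: Study design puts this before the intervention, yet patients are asked about a drug already received. The answer can only express expectation.
- Months 3 and 6: both precede the month-12 colonoscopy, so the colonoscopy result cannot influence them.
- Month 12: neither Study design, Study period nor Secondary outcome says whether the guess comes before or after the colonoscopy result is disclosed. If after, it could reflect recurrence as much as masking; if before, that problem does not arise.

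**The case against.** The strongest reply is that no route to unblinding is described. The section says that patients are asked, without naming who asks, and that the statistician records the results. The two trained researchers may collect the answers and the statistician may only log them off site. Information would then flow from patient to statistician. Nothing in the article sends allocation back to patients or to those who score symptoms, and the code is to be kept strictly confidential. This stands. A reader might infer that the blinding check itself breaks the blind, or that the double-blind claim can no longer be supported. The documents support neither inference: they describe no face-to-face questioning by the code holder and no leak to symptom assessors.

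A second reply is that a different statistician may be meant, since Statistical analysis also has professional statisticians entering data. That is possible. The wording favours one person but does not settle it, and if two are meant the text needs to say so.

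A third reply is that recording outside the site has a merit. If a site researcher recorded the guesses, the same researcher could hear a patient's guess and reasons while collecting subjective symptom scores. This stands too, and it rules out simply handing the task to the site data collectors.

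On timing, a baseline guess does no harm and can serve as a reference for expectation. A reader might also infer that the month-12 guess is contaminated by the colonoscopy result, but the order is not stated, so this is a point to settle and not an error.

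The reply that this is mere condensation does not stand. The article itself names the recorder, the code holder and the separation between them, and those statements conflict.

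**Conclusion.** The point holds as a conflict between role rules, with an avoidable risk of biased recording. A holder of the allocation table would record, at all four planned rounds, the outcome meant to show whether the blind succeeded, although the same protocol keeps that person out of the study's conduct.

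The conclusion rests on two assumptions: that the references to a third-party statistician mean one person, and that recording guesses counts as taking part in the study. The first is a natural inference from the wording; the second is hard to dispute for a listed secondary outcome.

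The size is limited. Up to 320 records are affected, but the amount of bias cannot be quantified from the documents and may be nil. The primary outcome, adenoma recurrence, depends on colonoscopy and pathology and is much less exposed than the symptom scores. The change is still worth making, because it removes the doubt at almost no cost. The month-0 point is one of labelling, and the month-12 point one of stating the order.

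**What to change.** 1. In Secondary outcome, have each patient complete the guess and any reason on a form that the patient seals. Name as handler someone who has no access to the allocation list and does not score symptoms. A data manager might serve, since the protocol already keeps data managers blinded.
2. In Randomization and in Allocation concealment and blinding, state that the code-holding statistician sees no participant data, including the guesses, until database lock. Limit the statement that statisticians are blinded to those who do not hold the code. If the agency supplies two statisticians, say so and separate their roles.
3. Keep the month-0 question if wanted, ask it as which treatment the patient expects, and report it as baseline expectation and not as evidence of blinding.
4. State that the month-12 guess is collected before the colonoscopy result is disclosed to the patient.

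The cost is revised wording, a sealed form and a small change in form handling. No extra staff, visits or patients are needed. Keeping the forms sealed and away from symptom scorers also preserves the one advantage of off-site recording.
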